### Experimental multimodal behavioral intervention (AAR + MBI)

Prior to implementing the experimental MBI, counselors will complete a 5-day Certified Tobacco Treatment Specialists training accredited by the Association for Treatment of Tobacco Use and Dependence. An additional 30 h of training by [name] (PI) will expand counselors’ skills including (a) how to guide TSE protection efforts as part of a cognitive behavioral therapy (CBT)-framed strategy to shape parents’ behavior toward a cessation attempt; (b) how to facilitate TSE protective behaviors and smoking behavior change in the context of challenges faced by low-income parents who smoke; and (c) how to drive a counseling process that integrates support and skills training with advice that facilitates participants’ mobile app usage to extend individualized treatment beyond phone sessions. Training in CBT strategies allows for tailoring counseling to participants based on identified barriers (e.g., other smokers in the home) and catalysts (e.g., concerns for child health) of behavior change. After intensive competency-based training, counselors will refine skills in ongoing weekly supervision that includes review of fidelity monitoring feedback, discussion of current cases, and role-playing of effective session interaction.

Intervention components were informed by the current literature and our two previous smoking trials with low-income parents [20, 21, 26]. Components include integrated health messaging that parallels WIC counselor advice as well as support and guidance with skills training and problem solving that is delivered via multiple treatment modes: (a) a project quitline that provides up to 5 telephone counseling sessions during the weeks between orientation and 3-month end-of-treatment phone assessment; (b) a research-ready BLiSS mobile app; (c) print materials for the participant and their family; (d) inter-session text follow-up, reminders and support as well as scheduled educational video clips that highlight telephone session and written materials content; (d) 8 weeks of NRT and instructional support.

At treatment orientation, staff will provide a printed participant guide to the intervention with treatment schedule and content that parallels upcoming counseling, and a printed family guide to BLiSS that suggests ways to navigate family-level barriers to child TSE adoption and smokefree home adoption. Counselors review materials such as behavioral contracts for a smokefree home, “no smoking” signs, information about the importance of NRT, and advice about proper NRT use. Counselors also download the BLiSS app to participants’ smartphones, oversee participants’ viewing of our app tutorial video and review a printed app instruction pamphlet.

#### Telephone counseling “quitline”

The quitline is the integral component within the MBI. Phone counseling is an emerging standard of care that is efficacious, acceptable and can reach disadvantaged populations [29–31]. NRT can also be distributed by quitlines [32]. The timing and frequency of telephone sessions is guided by best practices, including multiple proactive calling and at least 2–3 completed calls [29, 33, 34]. We plan to offer 5 proactive calls with flexible scheduling to promote TSE protections, to shape TSE reduction achievements toward smoking cessation, and provide the extra support for skills training needed in our target population. We will also send frequent reminder messages via text and voicemail. The counseling schedule and content mirrors strategies used in our previous trials [20, 26] and common evidence-based practices implemented in state and national quitline counseling models [32]. Counseling content is also guided by recent evidence and approaches that use motivational components to promote family-level support for and adoption of TSE protective behaviors among household members by capitalizing on parents’ desire to protect young children from TSE [35, 36]. Key counseling components in BLiSS include: (a) increasing motivation for smoking behavior change with collaborative, individualized treatment plans, support with goal setting, and guidance for building social support; (b) addressing addiction with education about NRT and proper use; (c) improving skills (e.g., self-monitoring) to identify smoking “triggers” and to manage smoking urges with compensatory CBT strategies; (d) improving cessation self-efficacy; and finally (e) coaching and feedback about participants’ BLiSS mobile app usage facilitated by a web-linked counselor portal (dashboard) to encourage real-time self-monitoring and coping skills training.

#### BLiSS mobile app

Quitline standard practice [33] encourages the provision of smoking cessation mobile apps. However, unlike the BLiSS app, few smoking cessation apps adhere to practice guidelines or link to evidence based treatment [37]. The BLiSS mobile app is a modified version of the National Cancer Institute's former Quitpal mobile app [38] that participants can use on iPhone and Android platforms. The app includes features that facilitate real-time self-monitoring of cigarettes smoked, child TSE and trigger/urge associations. Participants also enter their quit date, track health progress and can view information about health improvements related to TSE protection and cessation and a goal progress summary. The app also records times and triggers participants enter each day, and on subsequent days, pushes urge management strategies and reminders (e.g., NRT use) at those times to encourage motivation and provide supportive guidance and positive reinforcement of their efforts.

An innovative feature of the BLiSS app is the web-linked counselor portal with a dashboard that displays participant app usage. The dashboard guides supportive feedback from health counselors around self-monitoring without adding participant burden, thereby enabling “supportive accountability” which theory and empirical evidence suggest could facilitate more effective mHealth use [39]. Counselors will discuss and troubleshoot participants’ app usage to and provide positive reinforcement for their tracking efforts with the app. Such exchanges will increase intersession intervention dosage around individualized skills training.

#### Nicotine replacement therapy starter and instructions

NRT products will be provided to participants (specifically, nicotine gum, lozenge or patch). NRT is FDA approved for smoking cessation interventions and available over the counter. Following best-practice guidelines and practices implemented by state quitlines with low-income clients [32, 40], we will mail participants up to 8-weeks of free NRT prior to their quit day. Project quitline counselors will give advice on NRT use based on guidelines including benefits and harms, safe use and disposal.

#### Text messaging and educational video clips

To supplement written materials provided during the orientation and counseling messaging throughout treatment, we will also provide frequent text messaging. One purpose of text messaging is to remind and encourage participants’ adherence to scheduled telephone sessions. Another purposed is to extend messaging around key components of the behavioral intervention. This is achieved with brief, post session summary of primary individualized content and advice to emphasize intersession goals and skills training “homework.” Health messaging is also extended with 10 scheduled text messages with attached brief animated videos highlighting essential components of the intervention. Examples of video topics include: the importance of goal setting; setting up smokefree zones as a step toward a smokefree home; overview of coping skills to manage smoking urges; managing weight and worry; relapse prevention. In a further attempt to integrate health messaging and skills training across modes of intervention, we use avatars of our telephone counselors in our written materials and video clips. Text messages also are used to prompt adherence to using the mobile app.

### Measures

#### Outcome variables

Child TSE is the primary outcome and is assessed using two methods that yield continuous variables. First, via validated timeline follow-back assessment [41], parents will report the number of cigarettes to which the child is exposed each day during the 7 days prior to all assessment periods. Child cotinine will be collected in urine samples at home visits following each phone assessment. The secondary outcome is parent smoking status (1 = quit; 0 = not quit). During phone interviews at 3- and 12-month follow-ups, staff will obtain parent self-reported 7-day point prevalence abstinence and prolonged abstinence [42]. Self-reported point prevalence abstinence will be bioverified with salivary cotinine (Nicalert™) and expired CO at home visits following the telephone assessments.

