**Methods/Design:**

This trial uses a randomized two-group design with three measurement points: baseline, 3-month and 12-month follow-up. The primary outcome is bioverified child TSE; the secondary outcome is bioverified maternal quit status. Smoking mothers of children less than 6 years old are recruited from WIC clinics. All participants receive WIC system-level intervention based on the “Ask, Advise, Refer (AAR)” best practices guidelines for pediatrics clinics. It includes training all WIC staff about the importance of maternal tobacco control; and detailing clinics with AAR intervention prompts in routine work flow to remind WIC nutrition counselors to ask all mothers about child TSE, advise about TSE harms and benefits of protection, and refer smokers to cessation services. After receiving the system intervention, mothers are randomized to receive 3 months of additional treatment or an attention control intervention: (1) The multimodal behavioral intervention (MBI) treatment includes telephone counseling sessions about child TSE reduction and smoking cessation, provision of nicotine replacement therapy, a mobile app to support cessation efforts, and multimedia text messages about TSE and smoking cessation; (2) The attention control intervention offers equivalent contact as the MBI and includes nutrition-focused telephone counseling, mobile app, and multimedia text messages about improving nutrition. The control condition also receives a referral to the state smoking cessation quitline.

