### Aims and hypotheses

Aim 1: Test the hypothesis that a program integrating a WIC system-level “AAR” intervention with an intensive multimodal behavioral intervention (AAR + MBI) will be more effective in reducing child TSE (primary outcome) than a WIC system AAR plus an attention control intervention (AAR + Control). *Hypothesis 1:* Compared with AAR + Control children, those in the AAR + MBI condition will have significantly greater reductions in parent-reported daily TSE and child urine cotinine from baseline to 3- and 12-month follow-up.

Aim 2: Test the hypothesis that the multilevel AAR + MBI will be more effective at increasing maternal quit rates (secondary outcome) than AAR + Control. *Hypothesis 2:* Compared with the control group, mothers in AAR + MBI will have a significantly greater bioverified, 7-day point prevalence quit rate at 3- and 12-month follow-up.

Aim 3: Test hypotheses that changes in theoretically important variables will mediate the effects of AAR + MBI on child TSE and parent smoking outcomes. *Hypothesis 3*: Compared with parents in the AAR + Control condition, parents in the AAR + MBI condition will evidence greater increases in TSE protective behaviors, social support, urge management coping skills, and self-efficacy related to protecting child from TSE and quitting smoking from baseline to 3-month follow-up. In turn, these changes in mediator variables will account for between-group differences in TSE and cessation outcomes at month 12 (e.g., change in child cotinine from baseline to 12-month follow-up).

Aim 4: Explore factors that may influence outcomes and moderate intervention effects, including presence of other smokers at home, nicotine dependence, depressive symptoms, weight concerns, and intervention dosage as measured by quitline, NRT, and app usage.

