## Methods and Design

### Overview

This study uses a two-group (experimental vs. attention control), double blind randomized controlled design with three measurement points including pre-treatment baseline, 3-month (end of treatment) and 12-month follow-up. The target population is smoking mothers enrolled in Philadelphia, Pennsylvania’s WIC program – a community-based health system that serves over 70,000 low-income families annually. The primary outcome is bioverified child TSE and the secondary outcome is bioverified maternal smoking abstinence. The study design is guided by CONSORT criteria [27] and is approved by Temple University’s Institutional Review Board (protocol number 23188). In the clinics, WIC nutrition counselors will be trained to implement the Ask, Advise, Refer (AAR) [23] intervention for addressing child TSE and parental smoking. All smokers, including those who do not wish to be referred to the BLiSS trial, will receive the state quitline number, which also helps them to access NRT. Eligible consented mothers will complete baseline assessment and get randomized to receive one of the two interventions: (a) the multimodal behavioral intervention (AAR + MBI) which will include telephone-based quitline counseling that focuses on reducing child TSE and maternal smoking cessation, an integrated mobile app linked to a web-enabled counselor portal to facilitate self-monitoring, text messages and educational video clips related to smoking, and NRT; or (b) the attention control (AAR + Control) intervention that includes similar contact time AAR + MBI with telephone-based nutrition education, separate mobile app and text-message delivered educational video clips that focus on improving family nutrition.

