### Analytic plan

The predictor is intervention group (AAR + MBI vs. AAR + Control) and the two endpoints include child exposure (continuous primary outcome) and parent cessation (dichotomous secondary outcome). Primary analyses will use an intention-to-treat approach and missing data will be addressed using multiple imputation. In sensitivity analyses, we will perform complete case analyses and investigate the impact of data that is potentially missing not at random. We will compare child cotinine change scores between intervention arms using multilevel random-effects linear regressions in which we include randomization arm as a fixed effect and WIC clinic as a random intercept to account for potential clustering within clinic. Potential confounders (e.g., nicotine dependence) will be added as covariates as necessary. We will use multiple logistic regressions with random intercepts for clinic to compare bioverified self-reported quit status (yes/no) between randomization arms at 3 and 12 months. To investigate mediation pathways, we will use a structural equation approach with change in cotinine levels and parent quit status as the outcomes. We will ensure that the intervention is associated with the potential mediators (e.g., self-efficacy) and that the mediators are associated with the outcomes. We will also use cluster-adjusted bootstrap standard errors for assessment of the mediated effect in which the variables are measured in a temporal ordering consistent with a causal pathway. For moderation analyses, we will use random-effects multiple regression modeling the change in cotinine levels and parent quit status, using confounding variables as necessary.

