#### Power analysis

We chose our sample size so that we would have at least 85% power to detect between-group differences in the primary outcomes (3- and 12-month child cotinine). Using an estimate of 20% 1-year follow-up attrition based on the KiSS trial, we expect to have 298 participants at 12 months (372*80% retention = 298, or 149 per group). With 149 participants per group, we will have 85.7% power to detect an effect of 0.23 in the log cotinine change scores between randomization arms.

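### The primary outcome is stated in several incompatible ways, so one to four comparisons could be called primary and none is named as deciding

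*Protocol article*

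**What the plan says.** The article describes the primary outcome in six places.

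- **Abstract, Methods/Design:** "The primary outcome is bioverified child TSE; the secondary outcome is bioverified maternal quit status". One outcome, biologically verified, no time point.
- **Overview:** "The primary outcome is bioverified child TSE and the secondary outcome is bioverified maternal smoking abstinence". The same, again with no deciding visit.
- **Aims and hypotheses, Hypothesis 1:** children in the intervention arm are expected to show "significantly greater reductions in parent-reported daily TSE and child urine cotinine from baseline to 3- and 12-month follow-up". Two measures at two visits.
- **Outcome variables:** "Child TSE is the primary outcome and is assessed using two methods that yield continuous variables". The two methods are a seven-day parental count of cigarettes and urine cotinine.
- **Analytic plan:** "the two endpoints include child exposure (continuous primary outcome) and parent cessation (dichotomous secondary outcome". Exposure counts as one endpoint here. The model that follows is for cotinine: "We will compare child cotinine change scores between intervention arms using multilevel random-effects linear regressions". The visit that decides is not named.
- **Power analysis:** the sample size is meant to give "at least 85% power to detect between-group differences in the primary outcomes (3- and 12-month child cotinine"). Primary outcomes are now plural, cotinine only, at both follow-ups.

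**The concern.** These statements differ in two respects: whether parent report is part of the primary outcome, and whether 3 months, 12 months or both decide. Parent report is not a biological measure, so including it conflicts with the abstract and Overview. A reader can count one, two or four primary comparisons, and the count could be settled after results are known.

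The false-positive rate and the power of the trial both depend on that count and on whether any or all of the comparisons must succeed. The two measures also differ in kind. One is a biomarker. The other is self-report, given in the intervention arm by mothers who were counselled on this very behaviour. If the two disagreed, the text does not say which would decide.

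**Working it through.** **Inputs from the Power analysis:** 372 randomised, 20% attrition, an effect of 0.23 in log cotinine change, 149 per group, 85.7% power. **Not given:** alpha, sidedness, SD, and the correlation between tests. I assume two-sided 0.05 and show correlations from 0 to 0.9.

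**1. The plan's own figures.** Retention reproduces: 372 × 0.80 = 297.6, about 298, or 149 per group. The 85.7% cannot be reproduced from stated inputs. If 0.23 were a standardised difference, 0.23/√(2/149) = 1.985 and 1.985 − 1.960 = 0.025, which gives 51.0% power. So 0.23 is most naturally a raw log difference with an unstated SD. Solving SD = 0.23 / [(z for alpha + z for power) × √(2/149)], with √(2/149) = 0.1159 and z for 85.7% power = 1.067:

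- two-sided 0.05: 0.23 / (3.027 × 0.1159) = 0.656
- two-sided 0.025: 0.23 / (3.308 × 0.1159) = 0.600

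Both pairs return 85.7%. The document therefore does not show whether two cotinine tests had already been allowed for.

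**2. Number of primary comparisons under each statement.**

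- Abstract, Overview: one measure, visit open
- Outcome variables: two measures, visits open
- Hypothesis 1: 2 measures × 2 visits = 4
- Power analysis: 1 measure × 2 visits = 2

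**3. Error rate if any one test suffices, and power if both cotinine tests must succeed.** For k independent tests at 0.05, familywise error is 1 − 0.95^k: 1 − 0.95² = 9.75% and 1 − 0.95⁴ = 18.5%. Joint power for two independent tests is 0.857² = 73.4%. The correlated values come from one million simulated sets of equally correlated normal test statistics. Error is the share with any |Z| above 1.960. Joint power is the share with every Z + 3.027 above 1.960.

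| Correlation | Error, 2 cotinine tests | Error, 4 tests | Joint power, 2 cotinine tests |
|---|---|---|---|
| 0 | 9.75% | 18.5% | 73.4% |
| 0.3 | 9.5% | 17.4% | 75.2% |
| 0.5 | 9.1% | 15.6% | 76.8% |
| 0.7 | 8.4% | 13.1% | 78.7% |
| 0.9 | 7.0% | 9.4% | 81.7% |

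The joint-power column assumes that each cotinine test has 85.7% power. Every error rate shown exceeds 5%, and every joint power is below 85%.

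**The case against.** The strongest defence is that the text leans towards cotinine. The abstract and Overview require biological verification, Procedures says urine is collected for that purpose, the Analytic plan models cotinine, and the Power analysis sizes the trial on it. Saying that a construct is assessed in two ways need not create two confirmatory tests, and a scientific hypothesis joined by an *and* is not a decision rule. This stands in part: it makes cotinine the best candidate. It does not remove parent report from Hypothesis 1 or Outcome variables, and it does not choose between 3 and 12 months.

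A second defence is that a condensed article may leave multiplicity rules, alpha and the model for parent report to a fuller document. That is right, and their absence is not the point made here. What the primary outcome is, and when it is measured, is core protocol content. The article states it repeatedly and inconsistently.

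A reader might infer something stronger, that the trial must either inflate its error rate or fall short of its stated power. The documents do not support that. A single cotinine test, a fixed testing order, or a calculation already made at 0.025 would avoid both for cotinine. None of these is stated, and none is ruled out.

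A reader might also put a figure on splitting alpha over the two visits. With SD 0.656, power per test at 0.025 would be 78.4%. With SD 0.600 it would be the stated 85.7%. The SD is back-solved in both cases, so the cost cannot be determined.

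Nor can a joint power be given for all four comparisons, because the article gives no power for parent report. Finally, independence is only an outer bound: the tests use the same children, and the two cotinine changes share a baseline.

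**Conclusion.** The point holds as an inconsistency in core protocol content. Between one and four comparisons could be called primary, and none is named as deciding.

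The sizes are conditional. If any single test at an assumed two-sided 0.05 suffices, familywise error is about 7.0% to 9.75% for the two cotinine tests and about 9.4% to 18.5% for four. If both cotinine visits must succeed and each has 85.7% power, joint power is about 73% to 82%, against a stated minimum of 85%. The ranges cover correlations from 0.9 to 0 for error and from 0 to 0.9 for power; the true correlation is not given. The inconsistency itself rests on none of these assumptions.

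**What to change.** Before unblinding, name one primary endpoint: one measure at one visit. The natural choice is change in log urine cotinine from baseline to 12 months. It is biologically verified, it has the stated regression model, and the power calculation uses the sample retained at 12 months. Test 3-month cotinine next in a fixed order, only if the 12-month test is significant, and make parent-reported exposure secondary. If the sponsor prefers to keep both visits primary, state whether one or both must succeed and at what alpha.

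Align Aims and hypotheses, Overview, Outcome variables, Analytic plan and Power analysis with this choice, and state the alpha and SD behind the 85.7%.

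The cost is wording in the protocol, the analysis plan and, where it differs, the registry entry. With a fixed order, the first test uses the full alpha. If the 85.7% was calculated at two-sided 0.05, that test keeps it with 372 randomised. The downside is that the 3-month and parent-reported results can no longer support a stand-alone primary claim.
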